#### Subgroup Analyses

Analyses will be performed to (1) describe intervention engagement and attrition to explore potential differences by parental income and education, study site, and ethnicity; (2) conduct descriptive analyses to explore whether intervention effectiveness differed between children’s gender or sex in the treatment group; and (3) evaluate the dose-response relationship in the intervention group and improvements in children’s health-related outcomes at 10 weeks, 6 months, and 12 months. Intervention dose will be defined by level of intervention engagement.

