### Objectives

The primary objective of this study is to evaluate the effectiveness of the synchronous web-based FHLP intervention compared to an active control group in lowering BMI *z* scores in children (aged 8-12 y) with BMI ≥85th percentile for age and sex over a 12-month period. The secondary objectives include evaluation of the effectiveness of FHLP compared to the active control in improving lifestyle behaviors and health-related quality of life in children (aged 8-12 y) with BMI ≥85th percentile for age and sex, as well as parental self-efficacy and motivation to support their child’s healthy living behaviors. The trial hypotheses are that the FHLP intervention will result in significantly greater reduction in BMI *z* scores than the active control and that intervention participants will show greater improvements across all domains than those in the control group.

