## Methods

### Trial Design

This study is a single-blind randomized controlled trial (ClinicalTrials.gov NCT06777888) with a 2×4 design (Figure 1). Participating households will be randomly assigned in a 1:1 ratio to 2 groups: FHLP intervention and control. Data will be collected at 4 assessment time points: baseline (wk 0), after the intervention (wk 10), 6-month follow-up (wk 26), and 12-month follow-up (wk 52; Figure 1). The intervention will be delivered via video chat in 3 regions across Canada (British Columbia, the prairie provinces, and Ontario), with the central site located at the University of Victoria in British Columbia.

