### Sample Size

The parameters used for sample size calculation are based on the results of a published randomized controlled trial evaluating the effectiveness of a family-based intervention in reducing BMI *z* scores compared to control [33]. The required sample size was estimated at 232 children, using a 2-arm, parallel-group design with 80% power. On the basis of previous research [17,33], the attrition (loss at follow-up) is expected to be similar between the groups (20%). In sum, the trial aimed to recruit a study population of 278 participants, which accounts for an attrition rate of 20%. In practice, 270 participants were successfully enrolled.

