### Data Analysis

#### Overview

All analyses will be intention to treat and will include all participants with available data. Patterns of missing data in the study groups will be examined, and multiple imputations will be applied to address missing data if data are missing at random. Generalized linear mixed models will be used to compare the effectiveness of the 2 treatments in improving the primary outcome, BMI *z* score, over time. The models will include fixed effects for treatment group, time, and group×time interaction; in addition, they will adjust for baseline BMI *z* score and child’s sex. A random intercept will be included to account for within-participant correlations across repeated measures. Similar to the primary outcome analysis, generalized linear mixed models will be used to examine changes in secondary outcomes over time. Models will adjust for the baseline value of the outcome, child’s sex, and parent’s relationship to the child; in addition, a random intercept will be included to account for repeated measures.

Previous research has shown that parental involvement in child interventions can differ in ways that affect behavioral and weight-related outcomes [55]. Including this variable makes it possible to control for these potential sources of variability in the generalized linear mixed models.

In line with the sex- and gender-based analysis framework of the Canadian Institutes of Health Research [56], which encourages the thoughtful integration of sex and gender into health research, we have taken steps to reflect sex and gender considerations in our analysis plan. Specifically, we will adjust for child sex assigned at birth where biological differences may be relevant to health outcomes (eg, BMI trajectories). In the exploratory analysis, descriptive analyses will be conducted to explore whether intervention effectiveness differed between children’s gender or sex in the treatment group.

Engagement metrics will primarily be examined in subgroup and dose-response analyses. However, engagement may play a role in treatment effectiveness. Therefore, its potential inclusion as a covariate in secondary models will be explored. These exploratory analyses will help clarify the mechanisms underlying intervention impact.

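### The exploratory question of whether effectiveness differs by sex or gender is, as most naturally read, to be answered within the FHLP arm alone, which cannot separate a difference in effect from a difference in underlying change

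*Protocol article*

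**What the plan says.** Item (2) of Subgroup Analyses is to "conduct descriptive analyses to explore whether intervention effectiveness differed between children’s gender or sex in the treatment group". The Data Analysis overview repeats it as part of the exploratory analysis: "descriptive analyses will be conducted to explore whether intervention effectiveness differed between children’s gender or sex in the treatment group".

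The Objectives set the meaning of effectiveness, since the primary aim is to "evaluate the effectiveness of the synchronous web-based FHLP intervention compared to an active control group in lowering BMI" z scores. That is a contrast between arms.

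For the primary model the overview states: "The models will include fixed effects for treatment group, time, and group×time interaction". Sex enters as an adjustment covariate, and the reason given is to "adjust for child sex assigned at birth where biological differences may be relevant to health outcomes (eg, BMI trajectories"). No sex-by-group term and no sex-specific comparison of FHLP with control appears anywhere in the article.

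A concurrent control arm is available. Trial Design says: "Participating households will be randomly assigned in a 1:1 ratio to 2 groups: FHLP intervention and control".

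**The concern.** A difference in effectiveness between boys and girls is a difference between two FHLP-minus-control contrasts. Restricting the comparison to the FHLP arm replaces it with a difference in change from baseline between two groups that were not formed by randomisation. If boys and girls would change differently without FHLP, the restricted comparison reports that difference as differential effectiveness. It can also cancel a real difference in effect. The article allows for this possibility when it gives BMI trajectories as its reason for adjusting for sex. The control arm, which would remove the ambiguity, is left out.

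The stakes lie in interpretation. The article presents this analysis as part of its commitment to sex- and gender-based analysis, so its result may be read as showing which children benefit.

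**Working it through.** The article states no figure for this analysis, so there is nothing to reproduce. The point rests on algebra. The numbers after it only give a sense of scale.

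**What each comparison estimates.** For sex *s*, let m_s be the mean change under control and d_s the effect of FHLP versus control. Mean change in the FHLP arm is then m_s + d_s.

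- Girls minus boys within the FHLP arm: (m_g − m_b) + (d_g − d_b).
- Girls minus boys within the control arm: m_g − m_b.
- The first minus the second: d_g − d_b, the sex-by-group interaction.

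Only the last is a difference in effectiveness, and it needs both arms. The within-FHLP contrast equals it only if m_g = m_b, which FHLP data alone cannot check.

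**Illustration: equal effects, unequal underlying change.**

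Inputs from the article: 270 enrolled, 1:1 allocation, 20% expected attrition. Assumptions not in the article: attrition occurs as expected, the sexes split evenly, a two-sided 5% test is applied, and the normal approximation holds.

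- FHLP children followed: 270 × 0.80 / 2 = 108, or 54 per sex.
- SE of the within-arm sex contrast, in units of the SD of change: sqrt(2/54) = 0.192.
- For an underlying gap g with d_g = d_b, the chance that the within-arm contrast looks significant is Φ(g/SE − 1.96) + Φ(−g/SE − 1.96).

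| Underlying sex gap (SD of change) | Within-arm contrast looks significant |
|---|---|
| 0.10 | 8% |
| 0.20 | 18% |
| 0.18 | 16% |
| 0.36 | 47% |

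The last two rows are rounded. They correspond to gaps of 0.10 and 0.20 BMI z units if the SD of change is 0.55 (0.10/0.55 = 0.182; 0.20/0.55 = 0.364). That SD is also an assumption. The sex-by-group contrast would stay at 5% in every row.

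**Masking.** The Sample Size section states: "The required sample size was estimated at 232 children, using a 2-arm, parallel-group design with 80% power". If all 232 are evaluable and split evenly, each sex-by-arm cell holds 58. A true difference in effect of 0.37 SD, offset by an underlying gap of −0.37 SD, leaves a within-arm contrast of zero, which is flagged 5% of the time. The sex-by-group contrast would detect it 29% of the time.

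**Precision of the sex-by-group contrast, 58 per cell.**

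- SE: sqrt(4/58) = 0.263 SD, against sqrt(2/58) = 0.186 SD within one arm. The ratio is sqrt(2), about 1.4.
- Difference in effect detectable with 80% power: (1.960 + 0.842) × 0.263 = 0.74 SD. With 54 per cell it is 2.802 × sqrt(4/54) = 0.76 SD.

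**The case against.** **The wording may be loose.** Elsewhere the article calls the FHLP arm the intervention group, including in item (3) of the same sentence in Subgroup Analyses. In the overview's model description, *treatment group* names the two-level factor. Item (2) could therefore be a drafting slip, not a decision to drop the controls. This stands in part, and a reader should not infer that the control arm has certainly been excluded. The phrase still reads more naturally as one arm, and no comparison between arms by sex is described on either reading.

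**BMI z score is already standardised.** The primary outcome follows World Health Organization criteria, and eligibility is by percentile for age and sex. A reader might infer that ordinary growth differences at ages 8 to 12 are bound to appear as a spurious sex difference. The article does not support that: it says only that biological differences may matter, and standardisation reduces them. It does not guarantee equal change in children selected at or above the 85th percentile, and no such standardisation is described for secondary outcomes such as step counts and questionnaire scores.

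**The analysis is descriptive and exploratory.** No test, alpha level or decision is attached to it, so the percentages above describe a test that the plan does not specify. This stands, and it limits the stakes. It does not cure the problem, because a descriptive summary of one arm still describes a different quantity from the one named.

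**Model terms may be left to an analysis plan that is not shown.** This is fair for the exact terms. The restriction to one arm is stated text in two places.

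**Conclusion.** The point holds as a correction to an exploratory analysis. As most naturally read, both sentences name a difference in effectiveness and plan a comparison that cannot identify one. That conclusion follows from the article's own definition of effectiveness and needs no numerical assumption.

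The size depends on an unknown underlying sex difference. With 54 FHLP children per sex, a gap of 0.1 to 0.2 SD of change would look significant about 8% to 18% of the time when the effects are equal. Reaching 16% to 47% takes gaps of about 0.18 to 0.36 SD. That higher range should not be attached to a gap of 0.1 to 0.2 SD; it belongs to 0.10 to 0.20 BMI z units with an SD of change of 0.55.

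A reader might also infer that the trial's main result is compromised. It is not: the primary comparison of FHLP with control does not depend on this analysis.

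**What to change.** Change item (2) of Subgroup Analyses and the matching sentence in the Data Analysis overview, the one that introduces the exploratory descriptive analyses. The preceding sentence, on adjusting for sex, is sound and can stay. Suggested text:

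*Effect modification by child sex will be explored using both arms, by adding sex × group and sex × group × time terms, with the lower-order sex × time term, to the mixed model. The week-52 FHLP-minus-control difference will be reported for each sex, with the interaction and 95% confidence intervals. Results by gender will be presented descriptively for both arms. These analyses are exploratory and have low precision.*

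If the within-arm summary is kept, reword it as describing change by sex or gender within the FHLP arm, and do not call it a difference in effectiveness.

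No new data are needed, because the control-arm measurements are already collected and the article reports that analysis is still under way. The price is a wider interval: the SE is about 1.4 times that of the within-arm contrast, and only a difference in effect of about 0.74 SD would be detectable with 80% power at 232 evaluable children. The report should say so, so that a null interaction is not read as evidence of equal benefit.

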### Data Safety Monitoring

The University of Victoria Human Research Ethics Board considers this trial to be a minimal-risk behavioral intervention; therefore, a data safety monitoring committee will not be established.

### Ethical Considerations

#### Ethics Approval

This study has been approved by the BC Harmonized Ethics Platform (H20-00759).

#### Informed Consent and Assent

During the screening process, a research assistant will speak with parents and caregivers by telephone to inform potential participants about the trial. The research assistant will explain that a consent form will be provided along with the first set of research questionnaires. All participants will be provided with the research team’s contact information and will be encouraged to reach out if they have any questions or concerns after reading through the consent form.

Parent consent and child assent will be obtained electronically through the REDCap survey delivery system (refer to Multimedia Appendix 1 for the study consent form). To document ongoing consent, participants will be required to review and sign a copy of the consent form before accessing the parent and child surveys at each assessment time point (ie, baseline, 10 wk, 6 mo, and 12 mo). Participants may choose to discontinue their involvement at any time.

#### Compensation Details

Participants will receive grocery cards valued at CAD $25 (approximately US $18) for completing all questionnaires at each assessment point, for a total of CAD $100 (approximately US $72) incentive value over the study duration.

#### Harms or Risks to the Safety of Participants Involved in the Trial

The FHLP intervention is designed as a lifestyle behavior intervention. Participants will be exposed only to activities and information that are already readily available. The University of Victoria Research Ethics Board considers this trial minimal risk because it involves potential benefits for participants, with risks of harm that do not exceed those encountered in daily life.

Potential risks include emotional discomfort for children, such as stress or embarrassment related to research participation, particularly during weight measurement. To mitigate this, the research team will normalize the measurement as a “healthy growth check.” Research team members will also complete Balanced View BC training on minimizing weight bias and using sensitive language when discussing weight and measurements associated with weight and lifestyle behaviors [57]. In addition, research team members will receive training on scope of practice and appropriate referral procedures when issues are raised that fall outside the scope of practice of the FHLP (eg, signs of disordered eating or serious physical health concerns). Participants with such concerns will be encouraged to contact clinical health professionals.

To ensure that participants can safely participate in the physical activity component of the program, each parent or guardian will complete the Canadian Society for Exercise Physiology Get Active Questionnaire at enrollment. This is an evidence-based self-administered tool that will guide each participant’s caregiver to make an informed decision about the appropriateness of increasing their child’s physical activity [58].

#### Privacy and Confidentiality

Data collected will be deidentified for program evaluation, with participant names replaced by study ID numbers. Participants’ confidentiality and the confidentiality of the data will be protected by having no participant names on any of the data during analysis. Electronic files will be stored using participants’ unique ID numbers (ie, study ID) on a secure network drive at the University of Victoria that is accessible only to the principal investigator and research staff. Participant data will be destroyed 5 years after the final study publication.

## Results

This study was funded in January 2020, and recruitment began in January 2021. A total of 270 participants were enrolled. Data collection was completed in June 2025 and analysis is currently underway. Results are expected to be published in winter 2025.

## Discussion

### Anticipated Findings

This study aims to evaluate the effectiveness of the FHLP intervention compared to an active control group in improving BMI *z* scores and related health outcomes in children aged 8 to 12 years. On the basis of the study objectives, it is hypothesized that children in the FHLP intervention group will show greater reductions in BMI *z* scores than those in the control group over the 12-month period. In addition, improvements in secondary outcomes are anticipated, including healthier lifestyle behaviors, enhanced quality of life for children, and increased parental self-efficacy and motivation to support their child’s healthy living. The blended delivery model, which combines self-guided resources with web-based synchronous sessions, is likely to foster greater engagement and adherence, promoting sustainable behavior changes.

### Comparison to Previous Work

The FHLP intervention was designed based on the M-PAC framework for supporting behavior change through reflective, regulatory, and reflexive processes. Several previous randomized controlled trials, including studies focusing on families with children in the target age range, have demonstrated that the M-PAC framework can be applied to promote a healthy lifestyle in community-based interventions [26,59-62].

Compared to existing family-based lifestyle interventions, the FHLP curriculum addresses a key gap by targeting 5 different behavioral domains to support healthy living (ie, physical activity, healthy eating, sleep, media use, and mental well-being). This has been identified as a strength because the majority of family-based childhood obesity interventions address only activity and nutrition [63].

Previous studies have found that eHealth behavior interventions can be effective for childhood obesity management, with technology-based delivery increasing intervention reach and accessibility [64,65]. However, participant engagement has been noted as a challenge for remote delivery [66]. This trial proposes engagement strategies that include weekly live sessions with a group facilitator, branded kit materials, frequent communication with participants, and personal check-ins from delivery staff to mitigate retention challenges.

This trial is one of the first to examine the long-term impact of blended web-based family-based behavioral interventions for childhood obesity. A recent randomized controlled trial of a 10-week web-based lifestyle intervention found it effective in improving short-term health outcomes for children with overweight or obesity, including decreasing BMI *z* scores and increasing quality of life, diet, and daily physical activity immediately after the intervention; however, long-term effectiveness has yet to be investigated [67].

### Strengths and Limitations

The study has several strengths. First, the innovative blended intervention design combines the scalability and flexibility of internet-based programs with the benefits of real-time support through web-based synchronous sessions. This hybrid approach has the potential to address common challenges in traditional in-person or self-guided web-based programs, such as limited accessibility and engagement, respectively. Second, the program was developed in collaboration with community stakeholders and informed by feedback from pilot participants, ensuring its relevance and practical applicability. Third, the intervention is grounded in the M-PAC framework, a robust theoretical model that emphasizes intention formation, action control, and maintenance, supporting sustained behavior change. Fourth, the rigorous trial design, which follows best practices for real-world randomized controlled trials [68,69], including pediatric-specific recommendations applied to reduce the risk of bias [70], enhances the validity and reliability of the findings. Finally, the study incorporates comprehensive outcome measures, providing a holistic understanding of the program’s impact on both children and parents.

However, this study also has limitations. The reliance on parent-reported home measurement data for height, weight, and dietary behaviors may introduce error due to variation between different scales. Protocols for parent-report measure for child height and weight were adopted due to COVID-19–related restrictions at the start of the trial. Previous research has shown that parent measurements of height and weight can be effective in classifying child weight status in the absence of professional measurements [71] and that providing instructional guides may improve accuracy [72]. Therefore, participating parents will be instructed to measure children as accurately as possible and provided with a link to a US Centers for Disease Control and Prevention guide titled “Measuring Children’s Height and Weight” [35].

Despite these limitations, this study has the potential to significantly advance the field of childhood obesity management by providing evidence on the effectiveness of an internet-based intervention. The results will offer valuable insights into how web-based synchronous sessions can enhance engagement, support behavior change, and improve health outcomes. These findings will inform policymakers, health care providers, and community organizations on the development and implementation of scalable, flexible, and effective interventions for managing childhood obesity.

### Dissemination Plan

This study is founded on the principles of integrated knowledge translation with an actively engaged academic, community, and public health partnership guiding the development of the intervention, the research and evaluation questions, the interpretation of results, and dissemination [73].

It is anticipated that the group-level deidentified results of this trial will be shared through conference presentations, reports to community stakeholders, and academic publications. A range of knowledge translation tools will also be developed for the general public, including dissemination of the resulting publications and general study information via web-based platforms, including the University of Victoria Digital Health Lab website, and official social media channels.

